## Abstract

**Background:**

Cancer mostly affects older adults, causing a wide variety of diagnostic and therapeutic dilemmas. One of the most important moments in cancer patients is the hospitalization period, in which older patients usually remain bedridden for many hours and this may lead to the appearance of sarcopenia and disability.

**Methods:**

We present the research protocol for a randomized controlled trial that will analyze whether an intervention applied to older patients (≥ 65 years) who are hospitalized for acute medical conditions in an Oncology Department improves function. A total of 240 hospitalized older patients will be recruited in the Hospital Universitario de Navarra, Pamplona, Spain, and they will be randomized. The intervention consists of a multicomponent exercise training program that will take place for 4 consecutive days (2 sessions/day). The control group will receive usual hospital care, which will include physical rehabilitation when needed. The primary end point will be the change in functional capacity from baseline to hospital discharge, assessed with the Short Physical Performance Battery (SPPB). Secondary end points will be changes in cognitive and mood status, quality of life, fatigue, strength (dynamic and handgrip), pain, nutrition, length of stay, falls, readmission rate and mortality at 3 months after discharge.

**Results:**

Basal data of the patients included in the RCT are described. The foreseen recruitment will not be achieved due to the context of the Covid pandemic and the significantly different responses observed during the clinical trial in oncogeriatric patients compared to our previous experience in older adults hospitalized for medical reasons.

**Discussion:**

If our hypothesis is correct and shows that a multicomponent, individualized and progressive exercise program is an effective therapy for improving the capacity of acutely hospitalized older patients compared to usual care, a change in the current system of hospitalization may be justified in oncogeriatric patients.

## Abbreviations

ADLsActivities of daily livingAEAdverse eventsHUNHospital Universitario de NavarraEQ-5D6- EuroQol–5 Dimension questionnaireGVTGait velocity testKPSKarnofsky Performance StatusMNA-SFMini-nutritional assessment- short formRCTRandomized clinical trialsRMRepetition maximumSPPBShort Physical Performance BatteryTMTTrail Making TestVASVisual analog scales.

## Background

**T**he progressive ageing of society and the challenge posed by care for older adults has become a true urgency for all countries and health systems (1). One of the key points for the modification of these needs is the high prevalence of chronic diseases, including cancer. Furthermore, cancer mostly affects older adults, involving a wide variety of diagnostic and therapeutic dilemmas (2). In this context, the concept of vulnerability or frailty linked to the geriatric patient can be projected onto the cancer patient (3), where the role of sarcopenia is a particular determining factor (4, 5).

During the hospitalization period, it is very common the development of disability, which can irreversibly mark the life course of patients with cancer (6, 7). Almost 60% of patients remain bedridden during their stay for an average of 20 hours per day (8), results that can be extrapolated, at least partially, to cancer patients (9).

Although there is much evidence of the role of exercise in cancer patients (4, 5), a strategy related to the prevention of functional impairment in hospitalized oncogeriatric patients has not been fully developed. In recent years the number of studies investigating physical activity and exercise behavior of frail older adults is increasing (10). The European VIVIFRAIL physical exercise prescription model has been developed by experts worldwide in the field of physical activity and frailty (11, 12, 13, 14), and can be considered a milestone in this regard. Through a multicomponent exercise program, functional and cognitive impairment can be prevented even in hospital settings with very elderly patients and with a high burden of morbidity (11, 12, 13). Furthermore, the physiological mechanisms underlying the benefits of exercise in this population are not completely clear yet (14).

However, there are numerous nuances that make the implementation of similar models in hospitalized cancer patients a real challenge (15). Furthermore, the evidence for the management of geriatric cancer patients is limited by the scarcity of randomized clinical trials. Older adults are often excluded from early phase studies and randomized clinical trials (RCT) by restrictive inclusion criteria being only 1% of interventional trials older-patient-specific (16, 17).

Thus, the main aim of the present RCT will be to analyze the effects of short-term multicomponent exercise training on functional capacity outcomes in acutely hospitalized older patients with cancer.

## Methods/design

### Study Design and Setting

This study is a randomized clinical trial conducted in the Medical Oncology Department with patients older than 65 years of a tertiary hospital in Spain - Hospital Universitario de Navarra (HUN). The study follows the principles of the Declaration of Helsinki (18) and the protocol employs relevant standard items for clinical trials according to the SPIRIT 2013 statement (19) and follows the CONSORT statement (20) for transparent reporting. The trial is registered at ClinicalTrials. gov (NCT05424055), the status is recruiting, and the protocol was approved by the HUN Clinical Research Ethics Committee (PI_2020/7). All patients or their legal representatives provide written informed consent. Patient recruitment begin with the normal visit of the patient during hospitalization assessing for inclusion criteria and obtaining informed consent.

### Participants and eligibility

Patients are admitted to the hospital, to the Medical Oncology Department, regardless of the type of cancer, and usually in relation to complications related to their underlying disease or related treatments. Patients or their relatives (if the patient is unable to comprehend themselves) are informed of the random inclusion in one group but are not be informed which group the patient belongs to. The data for both the intervention group and the control group will be obtained at three different times: at baseline, before discharge, and at the 1-month followup.

The inclusion criteria are: age 65 years or older, Barthel Index score of 60 or more (scale, 0 [severe functional dependence] to 100 [functional independence]), being able to ambulate (with/without assistance), and to communicate and collaborate with the research team, and signing the informed consent form,. The exclusion criteria included are expected length of stay less than 6 days or more, terminal illness, very severe cognitive decline (ie, Global Deterioration Scale score, 7), uncontrolled arrhythmias, acute pulmonary embolism, acute myocardial infarction, and extremity bone fracture in the past 3 months. Inclusion and exclusion criteria are summarized in Table 1.

**Table 1 Tab1:** Eligibility criteria

**Inclusion**	**Exclusion**
• Women and men aged ≥ 65 years	• Expected length of stay < 6 days
• Barthel Index ≥ 60 points	• Terminal illness
• Able to ambulate (with/without assistance)	• Very severe cognitive decline (i.e., GDS 7)
• Sign the informed consent	• Uncontrolled clinical situations as unstable infections, arrhythmias, acute pulmonary embolism, acute myocardial infarction or limb bone fracture in the past 3 months, or any clinical condition considered by the attending doctor as innapropriate for the trial.
• Able to communicate	

GDS: Global Deterioration Scale

After randomization, the research team (physiotherapist, sport science specialist, oncologist, and geriatrician) perform the baseline measurement and follow-up visits of functional, pharmacological, comorbidity, and cognitive assessment, as well as mobility and strength evaluations (Table 2). The multidisciplinary research team has previous experience in functional geriatric assessment and in the prescription of exercise in frail older patients in different clinical settings (12, 21). Regarding oncogeriatric patients, our previous findings confirm that a multicomponent exercise program improves measures of physical/cognitive functioning and quality of life in older adults with lung cancer under adjuvant therapy or palliative treatment, and some systematic reviews identify the best options and challenges in these type of patients (43, 44, 45, 46).

**Table 2 Tab2:** Time of measurement of the different variables in each of the participants of the study

**Measurement**	**T1 Baseline**	**T2 After training or control period**	**T3 1-month post decharge**	**T4 3-months post decharge**
Categorical scale of pain	x	x	x	x
Handgrip strength	x	x	x	x
Barthel Index	x	x	x	x
Karnofsky's Index	x	x	x	x
Geriatric depression Scale of Yesavage (GDS)	x	x	x	x
Short Physical Performance Battery (SPPB)	x	x	x	x
Gait Velocity Test (GVT)	x	x	x	x
Dual-task (verbal and arithmetic GVT)	x	x	x	x
Maximal isometric force of handgrip	x	x	x	x
1RM (Leg press, Chest press and Knee extension)	x	x	x	x
Muscle power at 50 % 1RM in Leg press	x	x	x	x
Quality of Life (EQ-5D-5L)	x	x	x	x
EORTC QLQ-C30	x	x	x	x
Geriatric syndromes	x	x	x	x
Brief Fatigue Inventory	x	x	x	x
Trail Making Test part A (TMT-A)	x	x	x	x
Laboratory parameters	x	x		
Diseases considered grouped by ACG of Salisbury and CIE-10 codes	x			
Cumulative Illness Rating Scale for Geriatrics (CIRS-G)	x			
Falls	x	x	x	x
Mini Nutritional Assessment (MNA)	x	x		

1RM: 1 Repetition Maximum;

Basic sociodemographic and clinical data of the participants are collected in the baseline visit (Table 1). All adverse events, including those related exclusively to the exercise such as muscle pain, fatigue and general aches and pains, will be recorded in an “adverse events diary” during follow-up visits by the training and testing staff, and by self-report during the study period. The time at which different variables (primary and secondary) will be measured is detailed in Table 2. A blood sample will be taken on the days of the baseline and before discharge measurements.

The variables related to the tumor and the reason for, and evolution of admission will also be collected, distinguishing between toxicity due to chemotherapy (CTCAE v5.0), intercurrent medical complication, or neoplastic progression.

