### Participant-Selection and Consent Process

Participants are identified during the oncologist assessment process at admission to the Oncology Department. If they agree, they will be forwarded to a space reserved for signing the free and informed consent form, an interview, and initial evaluation with the study researchers.

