### Randomization, allocation concealment and Interventions blinding

Patients who meet the inclusion criteria are randomly assigned to the intervention or control group. Prior to randomization (http://www.randomizer.org), the attending oncologist review the absolute and relative contraindications to participating in the exercise program and will provide general information about the study. The allocation mechanism is carried out until 240 total patients are assigned. The assignment keys will be kept in a confidential file in the HUN and will be opened at the end of the study's analyses. To ensure masking, an alpha-numerical code will be assigned to each study group. This code is delivered to the associated researcher and is not revealed to the investigators in charge of processing the data until the analysis of the coded interventions is completed. Assessors of outcomes are blinded to patient data, including allocation at baseline and follow-up. Blinding is used for all laboratory analyses. Owing to the nature of the study, patients cannot be blinded to the exercise training modality. The study flow diagram is shown in Fig. 1.

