**Figure 1 fig1:**
[figure not shown]
Flow diagram of the Study Protocol

All interventions take place at the Oncology Department of HUN (Pamplona, Spain) site facilities. Standard medical care are provided to all participants in all groups. Participants are randomly assigned to the following groups:•Usual care group (control): Participants randomly assigned to the usual care group receive normal hospital care, including physical rehabilitation when needed.•Multicomponent exercise group (intervention): The intervention consists of a multicomponent exercise training program which include supervised progressive resistance exercise training, balance-training and walking for 4 consecutive days. During the training period, patients are trained in 20-minute sessions twice a day (morning and evening).

The supervised multicomponent exercise training program include upper and lower body strengthening exercises, tailored to the individual's muscle function, using weight machines and aiming for 2–3 sets of 8–10 repetitions at an intensity of 40–70 % of 1 repetition maximum (RM) (Matrix, Johnson Health Tech, Ibérica, S.L., Madrid, Spain) combined with balance and gait retraining exercises that will progress in difficulty and functional exercises, such as rises from a chair. The second part of the session consists of functional exercises such as knee extension and flexion, hip abduction, balance movements, and daily walking in the hospital. The resistance exercises are focused on the major upper and lower limb muscles. Each resistance training session includes two exercises for the leg extensor muscles (bilateral leg extension and bilateral knee extension muscles) and one exercise for the upper limbs (seated bench press). In each session, subjects perform a specific warm-up with one set of very light loads for the upper and lower body. The training protocol is shown in Figure 2. Participants and their family members are carefully familiarized with the training procedures in advance. During hospitalization, two evaluations are carried out; the first one taking place on the day of inclusion in the study and the second one on the 6th day after said inclusion.

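### The stated order puts baseline SPPB after randomisation in patients who cannot be blinded, leaving the change-from-baseline endpoint open to an avoidable, though undemonstrated, bias

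*Protocol article*

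**What the plan says.** Participants and eligibility gives the only explicit order between allocation and baseline: "After randomization, the research team (physiotherapist, sport science specialist, oncologist, and geriatrician) perform the baseline measurement and follow-up visits". The sentence points to Table 2, where SPPB, gait, handgrip, 1RM and the questionnaires are T1 items.

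Four other statements bear on it:

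- Randomization, allocation concealment and Interventions blinding: "Owing to the nature of the study, patients cannot be blinded to the exercise training modality".
- The same section: "Assessors of outcomes are blinded to patient data, including allocation at baseline and follow-up".
- Participants and eligibility, on patients or relatives: they "are informed of the random inclusion in one group but are not be informed which group the patient belongs to".
- Participant-Selection and Consent Process sends consenting patients for "signing the free and informed consent form, an interview, and initial evaluation with the study researchers", without mentioning randomisation. The text after Figure 1 dates the two in-hospital evaluations: "the first one taking place on the day of inclusion in the study and the second one on the 6th day after said inclusion".

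The primary endpoint is the change in SPPB from baseline to discharge (Abstract, Outcome Assessment). Statistical procedures plans a linear mixed model with time, group and their interaction.

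**The concern.** SPPB, gait speed, handgrip and 1RM depend on effort, and mood, fatigue, pain and quality of life are self-reported. If a patient already knows the arm when T1 is done, enthusiasm or disappointment can move these measures differently in the two arms. A talkative patient can also unblind the assessor.

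A baseline taken before allocation can differ between arms only by chance. One taken after it loses that guarantee. Because the endpoint is a change from that baseline, a distortion at T1 is carried into the estimated effect even if every later assessment is sound.

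**Working it through.** **1. The plan's own figure.** Statistical procedures gives SD 2.5, pre-post correlation 0.5, α 5%, power 90%, difference 1 point, 101 per group, and 120 after 15% loss.

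- Baseline-adjusted SD: 2.5 × √(1 − 0.5²) = 2.165. This gives 99 per group two-sided (100 with the t distribution), close to 101.
- Change-score SD: 2.5 × √(2 × (1 − 0.5)) = 2.5. This gives 132 (133 with t).
- Loss: 101 / 0.85 = 118.8, so 119 against the stated 120.

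The order of baseline and randomisation alters none of these figures.

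**2. How a baseline shift passes through.** Let knowledge of allocation raise the intervention arm's mean T1 SPPB by b relative to control, and let the true effect at T2 be δ. The model has a free group term, so it does not force equal baseline means. With complete data the group-by-time contrast at T2 is

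(difference at T2) − (difference at T1) = δ − b.

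The shift enters in full. Its sign may be either way.

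**3. Illustrative size.** The article gives no value for b, so 0.1 to 0.5 points is an assumption. For the change score at 101 per group, the standard error is 2.5 × √(2/101) = 0.352. The type I error is two-sided at a nominal 5%. The last column assumes a true 1-point effect and a shift that works against the intervention.

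| Assumed b | Share of 1-point target | b / SE | Type I error, 101 per group | Type I error, 34 per group | Power, 101 per group |
|---|---|---|---|---|---|
| 0.1 | 10% | 0.28 | 5.9% | 5.3% | 72.5% |
| 0.25 | 25% | 0.71 | 11.0% | 7.0% | 56.8% |
| 0.5 | 50% | 1.42 | 29.5% | 13.1% | 29.5% |

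The no-shift power to set against the last column is about 81%, the power of a change-score comparison at 101 per group. The 34 per group is one-third recruitment (Discussion): 240 / 3 = 80, or 40 per arm, less 15%. At that size the type I error rises less because the standard error is larger. The bias in points is the same.

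**4. Which T1 items are exposed.** Barthel ≥ 60 is an inclusion criterion and only patients who meet the criteria are randomised, so Barthel must be known beforehand. Comorbidity indices and diagnosis codes do not depend on effort, and laboratory analyses are blinded. The exposed items are the performance tests and the self-reports.

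**The case against.** The strongest reply is that both routes are already addressed: assessors are blinded at baseline, and patients are not told their group. The first part stands and limits the concern, since assessor bias at T1 is covered if the rule is kept. It does not control the patient's own effort, nor what a patient says to the assessor.

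The second part stands only in part. The two statements on patients can be read together: the arm is not announced and becomes obvious when training starts. A reader might infer that patients know their arm at T1, or that the two statements flatly contradict each other. The article supports neither: no section says allocation is disclosed before T1. Equally, no section says T1 is finished before the patient learns the arm, and patients and relatives are familiarised with the training procedures in advance.

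A reader might also take the consent section as stating the opposite order. It does not mention randomisation, and its evaluation could be eligibility screening or T1 itself. If it is T1, the sentence in Participants and eligibility is wrong and needs correcting.

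It may be said that baseline adjustment would halve the bias (0.5 × b at the planning correlation). That would be true with baseline as a covariate, and the sample size in fact fits such an analysis, but Statistical procedures names none.

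Finally, withdrawal between allocation and T1 is possible under the stated order. The article documents none, and with evaluation on the day of inclusion the window is probably short. It adds little.

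**Conclusion.** The point holds as a possible bias, not a demonstrated one. The article places the primary baseline after randomisation, concedes that patients cannot be blinded, and does not say that T1 precedes the patient's knowledge of the arm. Under the planned model any resulting baseline difference is carried into the effect one for one. At an assumed 0.1 to 0.5 points that is 10% to 50% of the target difference; neither this range nor a direction comes from the documents.

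The conclusion rests on the stated order being the one followed, and on some patients learning their arm before or during T1. It covers the effort-dependent and self-reported measures, not every baseline item. It should be fixed because the change is simple and later adjustment cannot fully repair a contaminated baseline, but nothing here shows that the data collected so far are biased.

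**What to change.** - State that T1 SPPB, the other performance tests and the self-reported measures are completed and recorded after consent and before the allocation is generated, or at least before it is disclosed to anyone in contact with the patient.
- Correct the opening of the sentence in Participants and eligibility, and align it with the consent section, the blinding section and the text after Figure 1.
- Keep the statement that patients are not told their group, but limit it to the period until T1 is complete. Deleting it would remove the only stated protection against patient knowledge at baseline.
- For patients already enrolled, report the order actually followed and add a sensitivity analysis comparing T2 SPPB between arms without the post-allocation baseline.

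**Cost.** Two steps are reordered and wording is changed; sample size is unaffected. A few patients will be assessed and then not randomised. The T2-only comparison gives up the baseline information, although at the planning values its SD (2.5) equals that of the change score. With 40 per arm its standard error is 2.5 × √(2/40) = 0.56, so the 95% interval is about ± 1.1 points. It can show whether the result leans on the baseline, but cannot rule out a shift of the size assumed here.

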
### Statistical procedures

The sample size calculation was performed using the GPower v. 3.1 software, adopting a significance level of α = 5%, a correlation between pre-and post-intervention values of the Short Physical Performance Battery (SPPB) of ϱ = 0.5 and a standard deviation for the SPPB of σ = 2.5, the required sample size to have a power of 90% to detect a minimum difference of 1 point between groups in the post–pre SPPB score is 101 patients per group. Taking an expected loss of patients at follow-up of 15% into account, the final sample size required is 120 per group.

The description of the sample by the group will be conducted using statistics such as means and standard deviations or medians and interquartile ranges for the quantitative variables, and frequencies and percentages for the qualitative variables. For comparisons between groups at baseline, t-tests or Mann–Whitney U tests will be used for continuous variables, depending on normality, which will be checked for each using the Kolmogorov-Smirnov test and normal probability plots, and the chi-square test or Fisher's test will be used for categorical variables.

To determine the efficacy of the intervention in the quantitative variables, such as the SPPB, we will use linear mixed models, using time, group and time and group interaction as categorical covariates. In the case of qualitative or categorized variables (such as whether an improvement of a given magnitude between pre-and post-intervention has been achieved or not), comparisons between groups will be conducted with the chi-square test or Fisher's test, and complemented with logistic regression if additional adjustment is needed. Effect sizes between-group will be computed based on Cohen's d and the 95% confidence interval. The level of statistical significance will be 0.05. Data will be analyzed using an intention-to-treat approach with R and SPSS statistical packages.

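### The reason for admission is recorded but left out of the stated SPPB model; adjusting for it as known before randomisation would give a modest, uncertain gain in precision

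*Protocol article*

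**What the plan says.** - **Population.** Under Participants and eligibility, patients are admitted to the oncology department "regardless of the type of cancer, and usually in relation to complications related to their underlying disease or related treatments". Exclusions narrow this, among them terminal illness and, in Table 1, several unstable conditions.
- **Data collected.** The same section says that tumour variables and both the reason for admission and its later evolution are collected, "distinguishing between toxicity due to chemotherapy (CTCAE v5.0), intercurrent medical complication, or neoplastic progression".
- **Allocation.** "Patients who meet the inclusion criteria are randomly assigned to the intervention or control group", using a web randomiser. No stratification factor is named.
- **Primary outcome.** "The primary end point will be the change in functional capacity from baseline to hospital discharge", measured with the SPPB (Abstract). The text under Figure 1 puts the first in-hospital evaluation on the day of inclusion and "the second one on the 6th day after said inclusion".
- **Analysis.** For quantitative variables such as the SPPB, "we will use linear mixed models, using time, group and time and group interaction as categorical covariates" (Statistical procedures). The only adjustment clause concerns categorical outcomes, which are "complemented with logistic regression if additional adjustment is needed"; it names no covariate.
- **Recruitment.** The Discussion reports one-third of the planned recruitment and power of almost 50% for a 1-point difference.

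**The concern.** Over an interval of about six days, SPPB change may depend partly on the acute problem that brought the patient in. If so, the reason for admission is prognostic for the primary outcome. With the stated model, variation between the three reasons stays in the residual, and a chance difference in case mix between arms is not corrected in the estimate. With about 80 patients instead of 240, such a difference can be noticeable and lost precision is costly.

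This is more than silence about a detail left to a fuller document. The article lists the terms of the SPPB model, and a variable that the trial chose to collect is not among them. Statistical procedures also plans significance tests of baseline differences and allows adjustment of categorical outcomes if needed. Together these leave room to choose covariates after imbalances have been seen.

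**Working it through.** **Inputs from the article** (Statistical procedures, Discussion): SD 2.5, pre-post correlation 0.5, difference 1 point, alpha 5% (two-sided assumed), power 90%, 101 per group, 15% loss, 120 per group. One-third of 240 is 80, or 40 per arm.

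**1. The plan's own figure.** n per group = 2 × (1.96 + 1.282)² × SD² / 1².
- Baseline-adjusted (ANCOVA): SD = 2.5 × √(1 − 0.5²) = 2.165, giving n = 99 (100 with the t distribution). This is close to the stated 101.
- Change score: SD = 2.5 × √(2 × (1 − 0.5)) = 2.5, giving n = 132 (133 with the t distribution).
- Loss: 101 / 0.85 = 119, against 120 stated.

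Both bases are carried forward, because 101 fits ANCOVA while a mixed model with free baseline means in each group behaves like a change-score comparison.

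**2. Power at 40 per arm without adjustment.**
- Change score: SE = 2.5 × √(2/40) = 0.56, power 43%.
- ANCOVA: SE = 2.165 × √(2/40) = 0.48, power 54%.
- With 34 per arm (40 × 0.85), the figures are 38% and 48%. The article's almost 50% is consistent with the latter.

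**3. Assumptions about case mix.** The article gives no shares and no SPPB change by reason. Assume three equal categories with mean changes +d, 0 and −d, so the range between best and worst is 2d. Assume also that the planned SD already contains this variation and, on the ANCOVA basis, that none of it is explained by baseline SPPB. Then:
- between-category variance Vb = (2/3) × d²
- share explained R² = Vb / SD²
- adjusted SD = SD × √(1 − R²)
- SD of the chance case-mix shift in the group difference = √(2 × Vb / n)

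**4. Results at 40 per arm.**

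| Range (2d) | Vb | R², change score | Power, change score | R², ANCOVA | Power, ANCOVA | SD of chance shift |
|---|---|---|---|---|---|---|
| none | 0 | 0 | 43% | 0 | 54% | 0 |
| 1 point | 0.167 | 2.7% | 44% | 3.6% | 56% | 0.09 |
| 2 points | 0.667 | 10.7% | 47% | 14.2% | 61% | 0.18 |
| 3 points | 1.5 | 24% | 54% | 32% | 71% | 0.27 |

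Unequal shares give slightly smaller gains. For a 2-point range, R² on the change-score basis is 8% with shares 25/50/25 and 9% with 40/40/20.

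**5. The chance shift in context.** It is a component of the standard error, not an addition to it. On the change-score basis, removing it takes the SE from 0.56 to 0.56 × √(1 − 0.107) = 0.53 for a 2-point range, and to 0.56 × √(1 − 0.24) = 0.49 for a 3-point range.

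**6. Validity without adjustment.** In 20,000 simulated null trials (40 per arm, d = 1, total SD 2.5), the unadjusted comparison had a type I error of 5.1% and a mean estimate of 0.005.

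**7. Form of the covariate.** A main effect of reason shifts a patient's baseline and follow-up equally and cancels from the change. Only its interaction with time can absorb differences in change.

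**8. Comparison within each reason.** With 40/3, about 13 per arm, SE = 2.5 × √(2/13) = 0.98 and the 95% half-width is 1.96 × 0.98 = 1.9 points.

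**The case against.** The strongest reply is that nothing here is an error. Time, group and their interaction make a standard randomised comparison that is valid without covariates, and a condensed article may leave further covariates or stratification to a fuller document. Broad eligibility is a legitimate choice. All of that stands. The point is a recommendation about a model whose terms the article does list.

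Stronger readings are tempting, but the article does not support them:
- **That case mix biases the result.** Randomisation keeps the estimate unbiased, and its standard error already covers chance imbalance (steps 5 and 6).
- **That case mix adds noise beyond the plan.** The source of the SD of 2.5 is not stated, and it may already include this variation.
- **That the three reasons have opposite natural courses.** The article does not say so and gives no data by reason. A range of 2 to 3 points would be two to three times the target effect; with 1 point the gain is only one or two percentage points of power.
- **That any reason for admission qualifies.** The exclusions begin with "terminal illness, very severe cognitive decline (ie, Global Deterioration Scale score, 7") and go on to several acute conditions. Table 1 adds unstable infections and anything the attending doctor considers unsuitable, and a Barthel Index of 60 or more and the ability to walk are required.
- **That the trial cannot tell non-response from a mix weighted to progression.** The concurrent control group shares the mix, so its natural course cancels on average. Differential response is a separate question of effect modification, which the added covariate does not test.

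One practical objection also stands. The article does not say when the reason is recorded, mentions it together with the later evolution of the admission, and places baseline measurement after randomisation. Patients are identified at the oncologist's assessment on admission, so the reason should be knowable beforehand, but the plan must say that this is the version used.

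**Conclusion.** The point holds as a modest efficiency recommendation, not as a flaw in validity. The stated SPPB model omits a collected variable that is plausibly prognostic over a short stay. Under the assumptions in step 3, the gain at 40 per arm ranges from negligible to useful: 1 to 11 percentage points of power on the change-score basis (43% to 44%–54%), and 2 to 17 on the ANCOVA basis (54% to 56%–71%, from unrounded values). The category shares, the range between reasons and the content of the planned SD are assumed, so the true gain could lie anywhere in these ranges or be close to nil. The recommendation is worthwhile because power is already about one-half and the data are being collected anyway. It holds only for the reason known before randomisation.

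**What to change.** In Statistical procedures, before unblinding and preferably before any comparison by coded group, specify that the primary SPPB mixed model includes as fixed effects the reason for admission (the three recorded categories) and its interaction with time. State that the category is the one known before randomisation, and that the later evolution of the admission, which can be affected by allocation, is not used for adjustment.

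The cost is one or two sentences and a few degrees of freedom: with three categories, 2 + 2 = 4 terms if the model covers baseline and T2 only, or 2 + 2 × 3 = 8 if it covers all four times in Table 2. If the reason proves weakly prognostic, little is gained and little is lost.

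A table of the SPPB difference within each reason is optional. It should be labelled descriptive, since intervals of about ±1.9 points at 13 per arm are too wide to show whether response differs by reason.
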